Hagen et al (submitted) conducted a RCT comparing MCT to a wait-list condition. Results from this trial demonstrated very large effect sizes for MCT. In this trial thirty-nine patients were randomly assigned to immediate MCT (10 sessions) or to a 10-week wait list period (WL). The WL-group received 10 sessions of MCT after the waiting period. Participants receiving MCT improved significantly more than the WL group with very large controlled effect sizes for both depressive ( $d = 2.51$ ) and anxious symptoms ( $d = 1.92$ ). Approximately 70-80% could be classified as recovered on the BDI-II at post-treatment and 6 months follow-up following immediate MCT, whilst 5% of the WL patients recovered during the waiting period. These findings suggest that a non-hybrid, pure version of MCT may be particularly effective.

The current proposed trial is designed to test MCT for MDD by comparing it to a bona fide benchmark treatment; CBT. The trial utilises a strict methodology intended to reduce potential biases encountered in earlier studies. Patients are allocated to a total possible number of treatment sessions with pre-set criteria for potential early termination. They receive up to 24 sessions of therapy or until they reach a predetermined agreed recovered state. Strict session-by-session manuals for both treatments, expert supervision in both CBT and MCT and objective definitions of recovery and relapse will be adopted using a conservative and clinical change index as defined by Jacobson and Truax (1991).

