### **Depressive symptoms (Hamilton Depression Rating Scale)**

The HDRS is a well-established and widely used rater-administered scale to measure the severity of depressive symptoms (Andrews & Williams, 2014; Hamilton, 1960; Williams, 1988). The scale consists of 17 items, which are grouped into different categories, such as depressed mood, suicide, insomnia, and somatic symptoms. Eight items are scored on a 5-point scale increasing in severity, where nine items are scored on a 3-point scale. The maximum score obtainable is 53. Scores of 0-17 indicates no depression, 8-13 indicates mild depression, 14-18 indicates moderate depression, 19-22 indicates severe depression, and above 23 indicates very severe depression.

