## **8. Safety Reporting and Adverse events**

An adverse event can be defined as:

*Any unfavourable, unintended effect that occurs during a study (e.g. symptom, diagnosis, test finding), having been absent at baseline, or if present at baseline appears to worsen.*

Information related to an adverse event will be captured in the case file and will be regularly monitored by the research management group in line with Good Clinical Practice Guidelines. In the case of adverse events like suicide attempts or sudden accidents it was decided to take action and report and exclude patients from the trial in order to get them hospitalised. However, no adverse events were reported in this trial.

A serious adverse event (SAE), is any untoward medical occurrence that

- results in death
- is life threatening (including suicide attempts)
- requires hospitalisation
- results in persistent or significant disability/incapacity

SAE's will be reported to the ethical committee that gave a favourable opinion to the study where in the opinion of the chief investigators the event was related to the research procedures. The response to SAE's will be determined on a case by case basis and will be in line with local policies and procedures.

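### Section 8 defines adverse events to include worsening from baseline, but its statement that none were reported rests on no described way of detecting worsening

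*Protocol*

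**What the plan says.** Section 8 of the protocol does three things.

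- **Definition.** An adverse event is "Any unfavourable, unintended effect that occurs during a study (e.g. symptom, diagnosis, test finding" and similar), with the condition "having been absent at baseline, or if present at baseline appears to worsen". No size or severity threshold is set.
- **Capture.** "Information related to an adverse event will be captured in the case file and will be regularly monitored by the research management group". The only examples are in a sentence on the response to events: "In the case of adverse events like suicide attempts or sudden accidents it was decided to take action and report and exclude patients".
- **Result.** "However, no adverse events were reported in this trial". No denominator, split by arm or method of enquiry comes with it.

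Elsewhere, the protocol schedules the measurements that bear on worsening. Appendix 2 places BDI-II at T1 (pre), at sessions, at T2 (post) and at T3 (follow-up), and HDRS at T1, T2 and T3. Section 6.1 describes HDRS content "such as depressed mood, suicide, insomnia, and somatic symptoms". Section 2 adopts the Jacobson and Truax change index for recovery and relapse, and aim 4 in section 3 concerns recovery rates and clinically significant change. None of these places links a score to harm.

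**The concern.** Every participant has major depressive disorder at entry (section 5.2), so worsening depression is the most obvious event that the definition covers. The capture route has no scheduled enquiry, no adverse event questionnaire and no rule that turns a worsened score into a recorded event. The examples are far narrower than the definition. A worsened patient enters the record only if someone chooses to write it down.

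The section then states a trial-wide zero, in the past tense, in a text that otherwise plans what will be done. A reader will take it as a safety result for both treatments under the broad definition printed just above it. Worsening depression and suicidality are central harms when two psychotherapies for depression are compared, so this is where a zero needs a stated basis.

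**Working it through.** **Passages side by side.** The document has no formula or count behind the zero, so there is no figure to reproduce. The check is whether definition, capture and result fit together.

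| Element | Scope in the protocol |
|---|---|
| Definition (section 8) | any new or worsened unfavourable, unintended effect, symptoms included |
| Capture (section 8) | case file, reviewed by the management group |
| Examples (section 8) | suicide attempts, sudden accidents |
| Scheduled scores (Appendix 2) | BDI-II at T1, sessions, T2, T3; HDRS at T1, T2, T3; not linked to section 8 |
| Result (section 8) | none reported |

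The result fits the examples. Nothing described would let it cover the whole definition.

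**How demanding a true zero would be.**

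Inputs: N = 128, the total in section 9.1 before the 20% increase for attrition. The proportion p of patients who worsen is not in the document and is an assumption, taken over 0.5% to 10%.

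Formula: P(no patient affected) = (1 − p)^N, taking patients as independent.

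- p = 0.5%: 0.995^128 = 0.53
- p = 1%: 0.99^128 = 0.28
- p = 2%: 0.98^128 = 0.075
- p = 3%: 0.97^128 = 0.020
- p = 5%: 0.95^128 = 0.0014
- p = 10%: 0.90^128 = about 0.000001

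Sensitivity to N: the 20% increase gives 128 × 1.2 = 153.6, so 154, or 128 / 0.8 = 160, depending on how it is read. At N = 154 the chance is 21% at p = 1%, 4.5% at 2% and 0.04% at 5%. At N = 160 it is 20%, 3.9% and 0.03%. The picture is the same.

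**The rate at which zero becomes unlikely.** Setting (1 − p)^128 = 0.05 gives p = 1 − 0.05^(1/128) = 2.3%. This is also the one-sided 95% upper bound from a fully ascertained 0/128. For one arm, 1 − 0.05^(1/64) = 4.6%. So even a complete and true zero would leave rates up to 4.6% per arm open. That bound concerns precision only and is no evidence about how events were sought.

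**The case against.** Several points on the other side are sound.

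- **Reported is not occurred.** A reader might infer that the protocol claims no adverse event happened. It says that none were reported, and that can be literally true.
- **A score is not automatically an event.** A reader might infer that any rise in BDI-II or HDRS above baseline is an adverse event. The definition speaks of an unintended effect and of a test finding, and a one-point fluctuation on a questionnaire does not plainly qualify. Worsening of depressive symptoms does.
- **No patient data are shown.** The document cannot prove that anyone worsened, so it does not support calling the sentence false. At a 0.5% or 1% rate, a true zero among 128 has a 53% or 28% chance.
- **Worsening is not invisible.** A reader might infer that a difference in deterioration between the arms would go unseen. BDI-II and HDRS are the primary outcomes, so worsened scores enter the comparison of the arms, and aim 4 covers clinically significant change. What is missing is any route by which worsening appears as harm.
- **The analysis plan is not shown.** Deterioration thresholds and harm tables are commonly left to it, and their absence from the protocol is not in itself a fault. But the definition, the capture route and the result sentence are all fixed in the protocol, and a later plan would not make them fit together.

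These points narrow the concern to ascertainment and wording. They do not remove the mismatch inside section 8.

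**Conclusion.** The point stands as an ascertainment gap. Section 8 includes worsening in its definition, describes no means of finding it, and reports a blanket zero. Read against that definition, the zero is plausible only if about 2% or fewer of the patients worsened. That figure rests on assumed rates, on independence between patients and on N of 128 to 160, because the protocol gives no rate.

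The documents do not support the stronger conclusions that events occurred and were missed, that the sentence is untrue, or that either treatment did harm. No sample size, power or alpha figure depends on this point. It is worth correcting because readers will take the sentence as a safety finding, and the data needed for a better statement are already scheduled.

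**What to change.** 1. Remove the result sentence from section 8, or limit it to the event types that were actually monitored.
2. State how events were sought (by whom, when, and by what enquiry) and whether worsening on BDI-II or HDRS counts under the definition.
3. Report by arm, with denominators and confidence intervals, the number and percentage of patients with reliable deterioration from T1 on BDI-II and on HDRS at the fixed T2 and T3 assessments. Use the Jacobson and Truax index already adopted, applied in the direction of worsening. Because section 8 provides for excluding patients after certain events, say how many patients in each arm lack T2 or T3 scores and why.
4. Add increases from T1 on the HDRS suicide item as a descriptive count by arm. A single item has no stated reliability threshold, so it should not carry a test.
5. Do not compare the arms on deterioration at any session. Section 1 ends treatment after two consecutive BDI-II scores of 8 or below, within a maximum of 24 sessions. The slower-responding arm would be measured more often and would collect more flags from exposure alone.

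The cost is a few sentences of protocol text and one extra table from data already scheduled, with no new visits and no change in sample size. The safety statement may become less favourable than the present one.

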## **9. Trial design and analysis**

The trial is a single blind randomised, parallel between-groups design with 6-months follow-up (See trial flow diagram and timeline [Trial Registration Number: ISRCTN82799488 - Meta-cognitive Therapy (MCT) versus Cognitive Behaviour Therapy (CBT) for Depression. An assessor will undertake HRSD ratings and will remain blind to treatment allocation. Randomisation lists will be drawn up independently and held outside of the study team.

Severity of depression and gender of participants will be used as stratification variables during randomization. Participants will be assigned to therapists within treatment modality based on therapist availability.

Patients will be allocated up to a maximum of 24 sessions of MCT or CBT and assessed at pre-treatment, mid-treatment, post-treatment and at 6-months follow-up.

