## **1. Lay Summary**

Major Depressive Disorder (MDD) is one of the largest health problems worldwide. Psychological treatments show variable outcome rates with approximately 50% recovery in 'gold standard' cognitive behaviour therapies (CBT's). More effective treatments for depression are needed. Metacognitive therapy (MCT) is a newer treatment for MDD that has produced promising results in preliminary studies. Hagen et al (submitted) showed very large effect sizes in a randomised trial comparing wait-list with MCT. In their study 70-80% could be classified as recovered. The next step is to compare MCT with CBT in a definitive trial.

In this study a large parallel randomised single-blind trial will be conducted comparing metacognitive therapy (MCT) and Cognitive Behavioural Therapy (CBT). Adult patients diagnosed with major depressive disorder (MDD) will be assigned to treatment consisting of up to 24 sessions of either CBT or MCT and the treatment terminated when remission is reached defined as two consecutive scores of  $\leq 8$  on Beck's Depression Inventory II (BDI-II). Patients will be followed-up for 6 months post-treatment.

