### **9.2. Randomisation and Data Analysis**

Randomisation will occur after initial pre-treatment evaluation by an external and independent person who holds a secret randomisation list produced by Manchester University. This list will be stratified for severity of depression (high/low) and gender (males/females). Scores on pre-treatment HDRS will be used to form four groups: 1) high severity ( $\text{HDRS} \geq 20$ ), 2) low severity ( $\text{HDRS} \leq 19$ ), 3) males and 4) females. Participants will be assigned to the two therapists (PC and SF) based on therapist availability.

A statistical Analysis Plan will be drawn up before study completion and the final data will be analysed by independent trial statisticians at The University of Manchester department of bio-statistics.

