## **12. Competency and treatment adherence**

In order to establish a fair and even level of competency and experience in CBT and MCT 24 patients were initially recruited to a pilot study (n=12 CBT, n=12 MCT) as training cases and not entered into the trial.

Treatment adherence and competency in both treatments is of vital importance. Highly experienced clinical psychologists PC and SF will deliver therapy. PC and SF have undergone specialist training and supervision in CBT with a minimum of ten years of clinical experience in the field. Leading senior psychologist and CBT therapist [name], with 35 years of CBT experience, will supervise the CBT condition and [name], the originator of MCT, will supervise the MCT treatment to ensure both treatments are delivered optimally and according to protocol.

All sessions will be recorded on videotape and screened by external psychologists [name] (SFN) and [name] (AL) for potential contamination of methods. Contamination is defined by the extent of ‘object-level’ work done in the MCT condition or ‘meta-level’ work done in the CBT condition..

20 random videotaped sessions (10 MCT and 10 CBT) will be selected and rated by final-year postgraduate psychology students for treatment adherence using the treatment fidelity checklists for CBT and MCT. To add an extra layer of quality checking to the CBT arm 10% of CBT tapes will be transcribed, translated and sent to external experts for evaluation of competency.

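### Patients go to one of two therapists by availability after allocation, and nothing balances therapist between arms, so a therapist difference can leak into an unadjusted MCT-CBT contrast

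*Protocol*

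**What the plan says.** Section 9 of the protocol states: "Participants will be assigned to therapists within treatment modality based on therapist availability". Section 9.2 repeats the rule for the whole trial: "Participants will be assigned to the two therapists", again "based on therapist availability".

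On timing, section 9.2 says "Randomisation will occur after initial pre-treatment evaluation by an external and independent person". It describes no booking of a therapist before that step. The list has two stratification factors, HDRS severity and gender. Therapist is not one of them.

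Section 12 covers delivery. The two therapists "have undergone specialist training and supervision in CBT with a minimum of ten years of clinical experience in the field"; no matching statement is made for MCT. It adds: "In order to establish a fair and even level of competency and experience in CBT and MCT 24 patients were initially recruited", 12 per treatment, none of whom entered the trial. It also provides expert supervision of each arm, recording of all sessions, and checks of contamination and adherence. These provisions imply that both therapists deliver both treatments, but no section says so.

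**The concern.** With only two therapists there is little averaging over providers. If one therapist's patients do better whatever the treatment, and that therapist carries a larger share of one arm, part of the therapist difference appears as a treatment difference. Randomising patients to arms does not prevent this, because the therapist is attached afterwards by a rule that is not random.

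The safeguards in section 12 address competence and fidelity. They may narrow the gap between the therapists, but they do not govern how many patients each one takes in each arm. At stake is whether an observed MCT-CBT difference can be credited to the treatment. A design in which both therapists treat in both arms is well suited to settle that, and the protocol neither requires it nor protects its balance.

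**Working it through.** **Inputs from protocol section 9.1.** Difference 4 BDI-II points (10 v 14), SD 7, alpha 5%, power 90%, 64 per group.

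**Assumed inputs, because the protocol gives none.** Difference between therapists, D: 1 to 3 BDI-II points. Difference between arms in one therapist's share of patients, s: varied below.

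**Step 1: the plan's own figure.** Two-sided normal approximation: n = 2 × (1.960 + 1.282)² × 7² / 4² = 64.4, so 65 per group. At 64 per group the power is 89.8%. The stated 64 is reproduced to within one patient, so this point does not rest on a sample-size error.

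**Step 2: bias formula.** Unadjusted bias = D × s.

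**Step 3: s if availability is unrelated to arm.** With an even split overall and 64 per arm, SD of s = √(0.25 × 2/64) = 0.088, and the 95% range is ±1.96 × 0.088 = ±0.17. The expected bias is then zero. At the edge of the range it is 0.17 × 1 = 0.17 to 0.17 × 3 = 0.52 points, about 0.2 to 0.5, or 4% to 13% of the 4-point target.

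**Step 4: effect on the test.** SE of the arm difference = 7 × √(2/64) = 1.24. For a given s and no true treatment effect, the false-positive rate is P(|Z + bias/1.24| > 1.96).

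| D (assumed) | s (assumed) | Bias (points) | Share of 4-point target | False-positive rate |
|---|---|---|---|---|
| 1 | 0.17 | 0.17 | 4% | 5.2% |
| 3 | 0.17 | 0.52 | 13% | 7.0% |
| 2 | 0.2 | 0.4 | 10% | 6.2% |
| 2 | 0.4 | 0.8 | 20% | 9.9% |
| 3 | 0.4 | 1.2 | 30% | 16.3% |

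The first two rows are the edge of chance imbalance. The last two need an imbalance that the rule permits but nothing in the protocol predicts.

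**Step 5: the limiting case.** If each therapist treated only one arm, s = 1 and the bias equals D. No analysis could separate the two.

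**Step 6: what adjustment costs.** If both therapists treat in both arms, a therapist term removes the therapist main effect. Variance inflation is 1/(1 − r²), where r is the correlation between arm and therapist. At 60/40 v 40/60, r = 0.2 and 1/(1 − 0.04) = 1.04, a cost of 4%. At 75/25 v 25/75, r = 0.5 and 1/(1 − 0.25) = 1.33, a cost of 33%.

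**The case against.** The strongest reply is that the problem can be handled in the analysis. If both therapists work in both arms, therapist and arm are crossed and a fixed effect removes the difference between them. Section 9.2 defers the analysis to a statistical analysis plan that is not at hand, so the absence of a therapist term from the protocol is no fault. This largely stands: the harm described is to an unadjusted contrast. Two things remain. Adjustment depends on overlap that the protocol never requires. And therapist is chosen after allocation by a non-random rule, so adjustment lacks the protection that randomising within therapist would give.

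Three stronger readings are tempting and are not supported.

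- A reader might take an imbalance of 75/25 v 25/75 with a 3-point therapist difference and infer a bias of 0.5 × 3 = 1.5 points, 38% of the target. That multiplies two worst-case assumptions. The protocol supports neither and gives no reason why availability should track arm. Section 12 (ten years' experience, pilot cases, supervision) makes a large therapist difference less likely.
- A reader might infer that the availability rule forfeits the crossed design. It costs precision, as step 6 shows. It does not forfeit the design unless the therapists fail to overlap.
- A reader might infer that choosing who treats whom makes the arms incomparable. Sorting patients between therapists after allocation does not change who is in each randomised arm. Only the overall therapist share, or an effect of matching patients to therapists, could shift the contrast.

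Finally, section 8 reports that no adverse events occurred, and the note to Appendix 2 reports a measure dropped after a printing error. Both suggest that the trial had already run when this text was written, so a change to the randomisation may come too late.

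**Conclusion.** The point holds as a cheap improvement to the design. It does not show that the result is biased. The protocol fixes a rule under which therapist can become unbalanced between arms, and it does not state that both therapists treat in both arms.

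If availability is unrelated to arm, the unadjusted bias is zero on average and at most about 0.2 to 0.5 BDI-II points at the edge of the 95% range. This assumes 64 per arm, an even overall split and a therapist difference of 1 to 3 points. Larger values are possible because the rule sets no limit, but the documents do not let anyone say how likely they are. The bias is small if caseloads are near equal or the therapists perform alike. It cannot be separated from the treatment effect if each therapist worked in one arm only.

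**What to change.** **If allocation is still open.** State that both therapists treat in both arms. Book each patient into a therapist slot by availability before the allocation is opened, then randomise to MCT or CBT within therapist, in small blocks. Include therapist as a fixed effect in the primary model. Availability still decides who sees whom, so the practical convenience is kept. The cost is a change in the order of two steps and one model term, with no extra patients or staff. The small downside is eight strata (2 × 2 × 2) instead of four, about 128/8 = 16 patients per stratum on average, which is why the blocks should be small.

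**Where allocation has already taken place.** Include therapist as a fixed effect in the primary model, tabulate therapist by arm, and limit the conclusion to delivery by these two therapists. If both treated in both arms, this recovers most of the benefit at the variance cost shown in step 6. If the table shows no overlap, the report should say that therapist and treatment cannot be separated.

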### **9.1. Sample size**

There are currently no direct comparisons of MCT against CBT for depression to inform sample size estimates. Therefore we plan the current study to detect a post-treatment difference between groups based on mean BDI-II scores observed in previous studies that tested MCT or CBT separately (Dimidjian, Hollon, Dobson et al, 2006; Papageorgiou & Wells, 2015). The mean following MCT was 10 and the mean for CBT 14, suggesting a group difference of 4 points (a standardized effect size of 0.57), we used 7 as the standard deviation (Papageorgiou & Wells, 2015). Using an alpha of 5% and 90% power, this indicated that 64 participants per group were required (total n=128). We plan to increase the target sample by a further 20% to allow for pre-to-post treatment attrition.

